## 11.1 Baseline and follow up data

### Primary outcomes

The co-primary outcomes are mental health (compositive measure PHQ-ADS) and quality of life (ICECAP-A) at 12-months.

### Secondary outcomes

- Patient Health Questionnaire Anxiety and Depression (PHQ-ADS), and ICEpop CAPability Measure for Adults (ICECAP-A), EuroQol Quality of Life (EQ-5D-5L)
- harmful substance use (Maudsley Addiction Profile (MAP), Leeds Dependence Questionnaire, (LDQ))
- risk taking behaviours (MAP)
- social functioning including occupation/education roles (MAP)
- physical health (MAP, EQ-5D-5L)
- housing status (self-report housing status)
- social outcomes, therapeutic alliance with the Peer Navigator (intervention group) and support workers (control group), and service accessibility (items from the Social Satisfaction Questionnaire (SSQ))
- service utilisation (MAP, self-report service utilisation (health, social care, and criminal justice), items from Client Evaluation of Self and Treatment (CEST))
- Relational empathy (Consultation and Relational Empathy measure (CARE))

Outcome measures will be assessed at baseline, and 6-, 12-, and 15-months post baseline allowing us to compare trajectories of outcomes during and after intervention between groups. The CARE

measure which asks participants about their relationship with their Peer Navigator (intervention condition) or Support Worker (control condition) will only be assessed at 6-, 12- and 15-months as participants will not have started working with the Peer Navigator at baseline. Excluding baseline data collection, a 12-week window (with six weeks either side) will be allowed for each data collection timepoint; given the characteristics of the target group we will seek to collect data wherever possible even if this is outside the 12-week window. The primary measurement point is 12 months post-baseline. The 15-month point has been included to gather information on whether there is any (rapid) post-intervention dissipation of intervention effects. This knowledge will be important for health/social care commissioners. Electronic data collection will be supported via a bespoke database with management tools designed by our Clinical Trials Unit CHaRT (University of Aberdeen). In the unlikely event of technical failure, the data will be collected using paper copies of the questionnaires.

Study Researchers, who are independent of intervention delivery, will collect outcomes from participants in face-to-face meetings where the database will be completed on study tablets by the researchers. Baseline demographic information will also be collected from participants including:

- participant age, gender, marital status, ethnicity, and disability status
- education
- Armed Forces experience and care system experiences
- medication use

Study researchers carrying out follow-up data collection at 6-, 12- and 15-months will also ask participants to update the contact information the research team hold about them and will complete a contact details form at each data collection timepoint.

## **11.2 Data transfer**

All data will be stored in line with General Data Protection Regulation (GDPR). The University of Stirling are leading and will be responsible for all process evaluation data and data collected from the Peer Navigators and staff. Only the research team at the University of Stirling who are involved in the day-to-day conduct of the study will have access to participants' identifiable information stored at the University of Stirling trial office. Anonymised and pseudonymised research data will be stored in secure SharePoint site for the study. Paper copies of consent forms will be scanned and saved in the SharePoint site and hard copies will be stored securely on site at the University of Stirling. Any identifiable data accessed outwith the University of Stirling campus will be password protected and shared only via a secure online system (i.e., audio files and transcripts being transferred to and by the transcriber). The research team will use an external transcriber (TP Transcription) who has signed a data protection/confidentiality agreement with University of Stirling. After each interview, the researcher will upload the recording from the audio recorder to the secure SharePoint site and immediately delete the recording from the audio recorder. Once the recordings are uploaded, they will be transferred to TP Transcription for transcribing and once transcribed and checked/pseudonymised, they will be deleted by the research team from the SharePoint site. Pseudonymised research data (i.e., transcripts) will be stored in the secure SharePoint site. Transcripts and consent forms will be stored for 10 years after the study has ended.

We will hold client and service staff participant contact details (name, address, phone number and email address if they have one) to contact them for data collection and dissemination purposes. These details will be stored in a separate password-protected Excel spreadsheet on the SharePoint site along with their unique reference ID. All data collected will be stored in password protected spreadsheets on the secure SharePoint site. Names and contact details will be kept for 24 months after the study has ended. After this point these details will be deleted.

The University of Aberdeen are leading and will be responsible for all client participant outcome measures data. These data will be collected as noted in the section above, on a bespoke data collection and management tool designed by the CHaRT research team. Data collection adheres to study specific operation manuals and SOPs. Once testing concludes, the CHaRT Senior IT manager or Senior Programmer issues a 'Database Authorisation to Go Live' form. This form signals the completion of testing, acceptance of validation sheets, and readiness for the database to go live. Intervention and control group participants will complete the outcome measures as noted in the sections above and these collected data will undergo pseudonymisation at the time of collection via an allocated participant ID number. No names or contact details will be recorded in the CHaRT data collection system.

As noted above, University of Stirling researchers will ensure that client participant names are logged on a separate spreadsheet (noted above) that is not connected to outcome measures data. This spreadsheet will have client participant names and contact details alongside their allocated ID number so that data collected across measure timepoints can be associated with that participant. Contact details are also needed because we aim to share study results with all participants. Copies of study results will be provided to all services and shared with intervention and control group participants.

Quantitative client participant outcome data will be hosted on the University of Aberdeen data centre. The University of Aberdeen provides and manages a resilient networked data storage solution which is replicated continuously to a disaster recovery site and backed up nightly. Strong network protection is provided in the form of isolation of services from each other and data stores. Access to the data is facilitated through a secure web application, the CHaRT data collection tool. Users, with pre-approved roles, need a username and password for entry, ensuring viewing or editing rights only for specific, location-based (centre) personal data. Access, being web-based, is location-independent. The website employs SSL/HTTPS with a minimum of 3DES SHA-1 encryption. Data will thus be linked to a pseudonymised ID number at University of Aberdeen, and all personal details will be stored securely at University of Stirling.

## **12. Safety**

The interests of all participants, including Peer Navigators and The Salvation Army staff, will be guarded by normal duties of care, following appropriate information and clinical research governance approval procedures.

### **12.1 Participants**

It is not expected that serious adverse events will result from taking part in the trial. However, given the vulnerability of people involved in the study, there will be a process for reporting and recording disclosures of current or future intent to harm themselves or others, or situations of actual / potential harm having taken place/at risk of taking place (this will be breaking confidentiality which is detailed on the participant information sheet and consent form for the study).

Most of the adverse events reported in the SHARPS study will be due to responses to a specific question in the PHQ-9 measure of depression which asks about suicidal thoughts or harm to self in the last 2 weeks. When this question is answered with any option other than 'not at all', the researcher is expected to inform staff in the service and complete an adverse events form for the participant. If such disclosures do occur, these will be shared by the researcher with service staff on the day of recruitment/data collection. Service staff will conduct a risk assessment as per their duty of care and The Salvation Army responsibilities. Researchers are not additionally required to verbally discuss such adverse events with the study leads unless they are seriously concerned about a participant's wellbeing.

An adverse events form describing the disclosure and the action taken will be completed by the researcher (with only the participant identifier code being recorded on the form) via the CHaRT data collection tool. These will all be notified electronically via the CHaRT website to the Study lead, Deputy Study Lead and Cluster Lead ([name]/[name]/[name]). They will also be notified by the researcher taking the disclosure to the Study Leads/Cluster Leads (above) via email. At the end of the recruitment/data collection day in service, the designated lead for adverse events (usually [name] but also [name]/[name] as needed) will go onto the study website and sign off on each of the adverse events from that day, checking that actions taken by researchers are appropriate.

At the end of each recruitment/data collection day in a service, the researchers will report the numbers of participants recruited to the study/who have done data collection to the cluster lead ([name]/[name]) who will then summarise the numbers to the Service Manager/Programme Manager. Any adverse events will be included in this email. The email will note the initials of the participants where there was an adverse event and what staff members were told about this (in line with the above) at the time. The participant initials and year of birth for individuals who have experienced an adverse event related to their response to the PHQ-9 in control service sites will also be reported The Salvation Army Senior Management in order for them to take forward safeguarding processes with control site service managers. There will be no other "more traditional" safety reporting of other adverse events within SHARPS.

Given that some participants may no longer be supported by The Salvation Army at 6-, 12- and 15-month follow up points, researchers will follow a different adverse events process for these individuals. If the participant reports thoughts of suicide/self-harm in response to the PHQ-9 or other issues, the data collector will remind them that they will have to inform the Study/Cluster leads about the disclosure. The researcher will also provide the participant with information about national/local support resources, including suicide helplines, via an information sheet at the end of the data collection session. The researcher will also tell the participant that a member of the study team will contact them (via phone, text and/or email) within 3 working days. If the data collector believes that the participant is in immediate danger, they will call the Police on 999. The data collector will then complete the usual adverse events form describing the disclosure and the action taken (with only the participant identifier code being recorded on the form) via the CHaRT data collection tool. An identified member of the study team will then contact participants within 3 working days to check in with them, ask them how they are feeling, and remind them of relevant services for support or to contact their GP. Three attempts will be made to contact the participant, if there is no response this will be recorded. The study team member will then log the participant contact and details of the call on a follow up risk assessment log stored on the SharePoint site. Co-investigators with specialist expertise in mental health will review the actions taken for all participants.

Any deaths will be recorded through the Change of Status, including cause and date of death where known.

## **12.2 Research staff and Peer Navigators**

We will take all reasonable steps to ensure staff safety. Researchers will undertake training including GCP training provided by NIHR, follow clear safety protocols, and should disclose any adverse events (e.g., violence and intimidation) they experience to the study leads and an adverse event form should be completed. All adverse event forms will be entered into the CHaRT data collection tool and stored electronically on the secure SharePoint. Risk assessments will also be conducted for the researchers throughout the study using university procedures. Any issues will be discussed with a member of the study team ([name], [name], [name]). Given the vulnerability of participants in the study, researchers will also be provided with additional training around suicide and reviewed, with additional support provided where required.

Peer Navigators will be provided with support and training around safety. Peer Navigators will be under the line management of The Salvation Army staff and will follow The Salvation Army procedures around adverse events and safeguarding reporting when working within the service. However, given that the role will involve outreach support to clients Peer Navigators should disclose any adverse events or safeguarding concerns they experience (including stalking, violence, intimidation, witnessing a crime, relapse) to their line manager within The Salvation Army immediately as soon as an incident occurs, contact the study leads and an adverse event form should be completed. Peer Navigators will also be encouraged to discuss issues arising from their role (e.g., clients encroaching on or testing boundaries, their own risk of relapse) in line management and clinical supervision. A lone working policy will be in place for Peer Navigators and lone working apps for phones will be provided where this is desirable for the Service Manager/Peer Navigator to have. Research staff will also have a lone working policy and risk assessment in place.

## **13. Statistical, health economic and process evaluation outcomes**

### **13.1 Primary outcomes**

Participant mental health (PHQ-ADS) and quality of life (ICECAP-A) at 12 months post baseline assessment.

### **13.2 Secondary outcomes**

#### *Trial participants*

Primary outcomes at collected 6- and 15-months post baseline assessment:

- Mental health (PHQ-ADS)
- Quality of life (ICECAP-A)

Secondary outcomes collected at 6, 12 and 15-months post baseline assessment:

- Harmful substance use (MAP, LDQ)
- Risk taking behaviours (MAP)
- Social functioning (MAP)
- Physical health (MAP, EQ-5D-5L)
- Housing status (self-reported)
- Social outcomes, therapeutic alliance with the Peer Navigator (intervention group) and support workers (control group), and service accessibility (items from the SSQ )
- Service utilisation (MAP, self-report service utilisations, items from CEST)
- Relational empathy (CARE)

#### *Peer Navigators and intervention service staff*

Collected at 6- and 12-months post baseline assessment:

- Normalisation Measure Development Questionnaire (NoMad)

#### *Peer Navigators & control site Support Workers*

Collected at 12 months post baseline assessment:

- Professional Quality of Life Scale (ProQoL)

- Job Satisfaction Survey (JSS)

### Safety

Collected throughout the trial:

- Number and proportion of adverse events
- Number of adverse events per participant
- Details of adverse events including seriousness

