## **14. Statistical considerations**

### **14.1 Sample size**

The unit of randomisation is city/town (the clusters), each cluster will recruit 25 participants (based on maximum possible caseload for each Peer Navigator) in the intervention arm and 30 participants in the control arm. A trial of 20 clusters will recruit 550 participants: we anticipate an attrition rate of up to 40% in the intervention arm and 50% in the control arm, based on feasibility work/related research resulting in outcome data on 300 participants (150 in each arm), equating to mean cluster size of 15. Assuming an ICC of 0.01 this design has 90% power to detect a 0.4SDs effect size. We will work our PPI collaborators to maximise retention in the study, refining processes as we go.

As part of the process evaluation, interviews will be undertaken with staff in the intervention services and with all the 10 Peer Navigators, to understand experiences of, and views on, the intervention from a range of perspectives, and to collect data on changes in the trial contexts during the study:

- Staff in a range of roles in intervention clusters (n=10)
- External stakeholders, including commissioning roles in intervention clusters (n=10)
- Staff in a range of roles in control clusters (n=10)
- Peer Navigators (n=20, i.e., all 10 Peer Navigators at two time points, pre and post intervention)

We will conduct the NoMad questionnaire [40] with a sample of staff (n=4-5) in each intervention setting at three time points (start, middle and end of intervention, aiming for a total sample size of 100-120).

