### **21.2 Archiving**

All study documentation will be kept for at least 10 years from the end of the study. Researchers obtaining consent will return consent forms and completed eligibility screening forms (ASSIST-Lite screening tool) to the SHARPS trial office in Stirling where they will be securely stored. If a potential participant did not meet the inclusion criteria (they score below the threshold on the ASSIST-Lite screening tool), all documentation will be shredded on The Salvation Army service premises and not returned to the trial office in Stirling. If electronic data collection is not possible, at the end of each participant's follow-up, Research Assistants will collect the data using paper copies of the questionnaires. Research Assistants are required to input any data they collect using paper copies into the CHaRT data collection tool as soon as the technical issue is resolved. Research Assistants will store any paper copies of anonymised participant data until they have finished collecting the participant data at that timepoint. A courier or tracked delivery will then be arranged to return any paper copies to the University of Stirling for safe storage. Adverse event forms and change of status forms will be completed and returned via email to the study leads at the University of Stirling ([name] and [name] for adverse events and [name] for change of status), or be entered electronically directly onto the SHARPS website database (where the University of Stirling team will be automatically notified by email). Research Assistants and Peer Navigators completing adverse event forms or change of status forms will also inform the study lead ([name]) or Deputy Study Lead ([name]) by phone call that a form has been completed and returned, if there is no response by email after 12 hours. If not captured electronically, once received, all adverse event forms and change of status forms will be recorded in the CHaRT tool by research staff at the University of Stirling. Where appropriate, the study leads at the University of Stirling will follow up with those reporting the incident to ensure that further action has been taken to ensure the safety of those involved. There will be no files stored at the trial sites, all files will either be stored on the SharePoint system, or securely within the University of Stirling or the University of Aberdeen.

Data will be archived by CHaRT for at least 10 years after the end of the study.

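### The count of adverse events per participant depends on completed assessments, which the plan expects to differ by arm, and deaths are not a listed safety outcome

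*Protocol*

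**What the plan says.** The Safety list in section 13.2 names three summaries: the number and proportion of adverse events, "Number of adverse events per participant", and details including seriousness. The capture period is "Collected throughout the trial". No denominator is given for the proportion or for the per-participant figure.

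Section 12.1 explains where events come from: "Most of the adverse events reported in the SHARPS study will be due to responses to a specific question in the PHQ-9 measure of depression". Any answer above the lowest category leads to a form, and the section rules out other conventional adverse event reporting. Section 11.1 and Table 1 place the questionnaire at baseline, 6, 12 and 15 months.

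Section 14.1 anticipates an "attrition rate of up to 40% in the intervention arm and 50% in the control arm", with 25 recruits per intervention cluster and 30 per control cluster.

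On deaths, section 12.1 says: "Any deaths will be recorded through the Change of Status, including cause and date of death where known". They do not appear in the Safety list of section 13.2.

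Section 12.2 also asks researchers and Peer Navigators to report adverse events that they themselves experience. It sends all adverse event forms to the same data collection tool.

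**The concern.** An event that is mainly a questionnaire answer needs an assessment at which to occur. A participant who is not seen cannot produce one. In a count per recruited participant, a missed visit therefore looks the same as a visit with no event. The plan expects fewer missed visits in the intervention arm, so this summary can differ between arms even if risk does not.

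Baseline answers add events that cannot be due to the intervention, because section 7.1 adds participants to the Peer Navigator caseload only after baseline data collection.

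The safety data go to the Trial Steering Committee and the Data Monitoring and Ethics Committee (section 14.2) and will be published. A retention artefact could be read as a hint of harm, or could hide one. Death, the least ambiguous harm, has no named comparison between arms.

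**Working it through.** **The plan's own figures.** Recruits are 10 × 25 = 250 and 10 × 30 = 300. With 40% and 50% attrition, 250 × 0.6 = 150 and 300 × 0.5 = 150 are observed, as section 14.1 states. The design effect is 1 + (15 − 1) × 0.01 = 1.14, so the effective size is 150 / 1.14 = 131.6 per arm. Power for 0.4 SD (two-sided 5%, normal approximation) is 0.9005, which agrees with the stated 90%. The attrition inputs are therefore read as the plan intends.

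**Assumptions, because the protocol gives no figure.**
- The probability p of a positive item at an assessment is the same in both arms and at every visit. A value of 0.3 is used for illustration, with a range of 0.2 to 0.5.
- All recruits complete baseline.
- Follow-up completion at 6, 12 and 15 months is either constant (60/60/60% v 50/50/50%) or falls linearly to 12 months and then holds (80/60/60% v 75/50/50%).
- Only events from the PHQ-9 item are modelled.

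**Formulas.** Events per recruit = p × expected completed assessments per recruit. Total events = recruits × events per recruit.

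| Pattern | Assessments per recruit, intervention v control | Ratio | Events per recruit at p = 0.3 | Total events at p = 0.3 |
|---|---|---|---|---|
| Follow-up only, constant | 1.8 v 1.5 | 1.20 | 0.54 v 0.45 | 135 v 135 |
| Follow-up only, linear | 2.0 v 1.75 | 1.14 | 0.60 v 0.525 | 150 v 157.5 |
| With baseline, constant | 2.8 v 2.5 | 1.12 | 0.84 v 0.75 | 210 v 225 |
| With baseline, linear | 3.0 v 2.75 | 1.09 | 0.90 v 0.825 | 225 v 247.5 |

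For example, 3 × 0.6 = 1.8 and 3 × 0.5 = 1.5; then 0.3 × 1.8 = 0.54 and 250 × 0.54 = 135, against 0.3 × 1.5 = 0.45 and 300 × 0.45 = 135.

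**Dependence on p.** It cancels from the ratio when it is the same at all visits. In the first pattern, p = 0.2 gives 0.36 v 0.30 and p = 0.5 gives 0.90 v 0.75, again a 20% excess. If positive answers are commoner at baseline than later, the excess in the two patterns with baseline is smaller than shown.

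**Direction of the two summaries.** In the third pattern the intervention arm has fewer events in total (210 v 225) but more per recruit (0.84 v 0.75), although the risk is identical by construction.

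**With completed assessments as the denominator**, each arm gives p and the ratio is 1.00 in every pattern, provided risk is equal among those seen.

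**The case against.** The protocol does not say that the denominator is recruited participants. Denominators for safety tables are commonly set in the statistical analysis plan, which is not shown here. With participants followed up as the denominator, the distortion would shrink or vanish. The attrition figures are upper limits for the sample size, and applying them at 6 and 15 months is an assumption. The committee reports also cover data collection and data quality (section 14.2), so completion by arm should be visible next to the events. These points limit the size and certainty of the effect. They do not remove it, because the protocol itself names a per-participant summary for an event that depends on visits and expects visits to differ by arm.

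Four stronger readings are tempting, but the documents do not support them.

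- **That the intervention arm will show more events, or will look harmful.** Totals are equal or higher in control, because more participants are recruited there.
- **That the excess is simply 20%.** That is the top of the range. It leaves out baseline events and applies the full attrition already at 6 months.
- **That Peer Navigators will inflate participant events in one arm.** Section 21.2 does mention "Research Assistants and Peer Navigators completing adverse event forms or change of status forms", but it concerns how forms are returned. Section 12.2 shows that the Navigators' forms mainly concern events that they experience themselves. What remains is that section 13.2 does not keep such forms apart from participant events.
- **That deaths go unrecorded.** They are recorded, with cause and date where known. They are only missing from the list of outcomes.

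**Conclusion.** The concern holds for the per-participant summary. At equal risk and with the planned attrition, a rate per recruited participant would be about 9% to 20% higher in the intervention arm, while raw totals would range from equal to 10% higher in control (247.5 / 225 = 1.10). The size rests on attrition reaching its stated upper limits, on the assumed retention pattern, on a common p across arms and visits, and on recruits being the denominator. The direction follows whichever arm is better retained, and the artefact disappears if retention is equal.

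Separately, deaths are collected but are not a listed safety outcome. Both gaps can be closed without new data, and a clearer summary than the one listed is available.

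**What to change.** In the Safety list of section 13.2:

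- Report the proportion of completed post-baseline PHQ-9 assessments with a positive item, by time point and arm, with the number assessed. Show baseline positives separately.
- Keep adverse event forms about events experienced by Peer Navigators or researchers (section 12.2) out of the participant count.
- Add deaths by arm over all recruited participants, taken from the Change of Status forms.
- Show assessment completion by arm beside the safety table.

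The last item addresses the one weakness of the change. A per-assessment proportion still describes only those who attend, and section 14.6 itself doubts that data in this population are missing at random. The change removes the arithmetic artefact but not selection by attendance.

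The cost is wording and table shells; all the data are already collected.
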